## Abstract

**Background:**

The prevalence of non-communicable diseases (NCDs) is increasing worldwide, also among children. Information about primary prevention of NCD’s is increasing; however, convincing strategies among children is needed. The present paper describes the design and methods in the Health Oriented Pedagogical Project (HOPP) study. The main objective is to evaluate the effects of a school-based physical activity intervention program on cardio-metabolic risk factors. Secondary objectives include assessment of physical, psychological and academic performance variables.

**Methods:**

The HOPP study is a 7 years longitudinal large-scale controlled intervention in seven elementary schools (*n* = 1545) with two control schools (*n* = 752); all aged 6–11 years at baseline. The school-based physical activity intervention program includes an increase in physical activity (PA) of 225 min/week as an integrated part of theoretical learning, in addition to the curriculum based 90 min/week of ordinary PA. Primary outcomes include cardio-metabolic risk factors measured as PA level, BMI status, waist circumference, muscle mass, percent fat, endurance test performance, total serum cholesterol, high-density lipoprotein (HDL), non-HDL, micro C-reactive protein (mCRP) and long-term blood sugar (HbA1c). In addition, secondary outcomes include anthropometric growth measures, physical fitness, quality of life (QoL), mental health, executive functions, diet and academic performance.

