#### Main outcome measure

In the present study cardio-metabolic risk factors were calculated by integrating objective measurements of BMI, waist circumference, muscle mass, percentage fat, endurance test, total serum cholesterol, HDL, non-HDL, mCRP and HbA1c. Firstly, all variables were divided into quartiles. Secondly, the results were dictomised as the children in the quartile of highest risk factor were given the score 1, and the children in the other quartiles were scored 0. Thirdly, children categorise with risk factors were assigned to one of 11 risk factor categories, 0–10, depending on their number of risk factors. Fourthly, the probability of children having 0 to 10 risk factors were calculated using the binominal probability formula (*n*! • *p*
^r^ • (1 – *p*)^*n-r*^ / (*r*! • (*n*-*r*)!) [49]. Where *n* is the possible number of risk factors (total of 11), *p* is the probability of having a risk factor (highest risk factor quartile: 0.25) and *r* is the number of risk factors for which the probability is calculated (0–10) [17]. Fifthly, the observed number of children in each group was compared to the expected number by calculating the ratio and plotting with a 95% confidence interval. Finally, a composite cardio-metabolic risk factor profile was calculated using Z-scores by age and gender for selected risk factors. The Z-scores were then summed for each individual regarding the individual risk factors to create the clustered risk score [17].

The occurrence of cardio-metabolic risk factors in the HOPP study was calculated at baseline. In addition, the calculus is to be computed annually to reveal any change in cardio-metabolic risk factors as a result of the intervention.

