##### Intervention analyses

Annually analyses between intervention and control schools in numerous variables, the sample size for a parallel group design is calculated using *n* = 2 • (σ / Δ) ^2^ • *k* [26]. Here n represents the number of participants in each group, σ (sigma) is the expected standard deviation of the observations (which are assumed equal for all groups), Δ (delta) gives us the relevant difference between observations, and k is the constant in this study chosen based on the common values by a double-sided t-test set at 5% and with test strength 80% (this corresponds to a *k* of 7.9) [26]. Based on these calculations we have determined the sample size to be adequate for all variables for all ages, also when divided into gender (Table 3).

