#### Analyses of longitudinal effect

The longitudinal intervention design allows for exploratory analysis of group means over time to discover patterns of systematic variation across groups, as well as among individuals. The design allows for analyses of age and growth effects [50]. As the eldest pupils enrolled at baseline 2015 finish elementary school in 2016, only one year of follow-up is possible. However, an increasing number of years of follow-up are possible with decreasing age at enrolment. This allows for an adjustment of the longevity of being enrolled in the program, and hence measurement of the time-in-the-program effect. Secondly, an annual comparison between the intervention schools and the control schools allows for testing of effect of the intervention. Thirdly, mean values across test time allows for time slopes showing possible effect as an interaction (i.e. effect modification) of intervention and time. A different approach for test across test time may be pre-post analysis of a single follow-up response in conjunction with a baseline measurement [50]. Fourthly, an annual comparison with the upcoming grade within the intervention schools allows for analyses of secular trends.

The longitudinal design in the HOPP study with repeated measures allows for use of a linear mixed regression model using test-year, years of follow-up, intervention versus control school, age and gender as fixed factors for the main outcome of cardio-metabolic risk factors. A similar model may be used for secondary outcomes of academic performance, PA level, cognitive performance, as well as medical and physical results, and simultaneously controlling for baseline values. In addition, the design admits analyses of interaction (i.e. effect modification) between type of intervention group and number of years in intervention.

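### The protocol gives three different accounts of what is primary, places PA level differently in each, and fixes no primary follow-up time

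*Protocol article*

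**What the plan says.** Four places in the protocol article bear on the primary outcome.

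- **Abstract, Methods.** The list opens "Primary outcomes include cardio-metabolic risk factors measured as PA level, BMI status, waist circumference, muscle mass, percent fat, endurance test performance" and continues with "total serum cholesterol, high-density lipoprotein (HDL), non-HDL, micro C-reactive protein (mCRP) and long-term blood sugar (HbA1c". That is six plus five, or eleven variables, and PA level comes first.
- **Main outcome measure.** The outcome is formed from "BMI, waist circumference, muscle mass, percentage fat, endurance test, total serum cholesterol, HDL, non-HDL, mCRP and HbA1c": ten variables, without PA level. Two measures follow. One counts the variables on which a child falls in the worst quartile (0 to 10). For the other, "a composite cardio-metabolic risk factor profile was calculated using Z-scores by age and gender for selected risk factors", and the scores are then summed. The selection is not given. The binomial formula for the count sets the number of possible risk factors at 11. The calculation is to be repeated every year.
- **Intervention analyses.** The text foresees "Annually analyses between intervention and control schools in numerous variables", with sample size based on a two-sided 5% test and 80% power.
- **Analyses of longitudinal effect.** A linear mixed model is offered for the main outcome, written as a single item. Then: "A similar model may be used for secondary outcomes of academic performance, PA level, cognitive performance".

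On timing, Analyses of effect describes a one-year comparison of 2015 with 2016. The Main outcome measure and Intervention analyses sections describe annual comparisons. Analyses of longitudinal effect describes slopes over time and, as an alternative, a single pre-post analysis. None is named as primary.

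**The concern.** Which outcome is primary, and when it is assessed, is a protocol decision. Here the text addresses it in several places and the answers differ. PA level is primary in the abstract, absent from the main outcome definition, and secondary in the longitudinal section. The main outcome itself has two forms, and one of them rests on an unstated selection of factors.

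At stake is what a later report may call the primary result. With the text as it stands, a report could present a single component, the risk-factor count or the Z-score, at one year or later, and cite the protocol for it. The error rate attached to the trial's main claim depends on which of these readings applies.

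**Working it through.** **1. The three lists side by side**

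| Place | Variables | PA level |
|---|---|---|
| Abstract, Methods | 6 + 5 = 11, called primary | primary |
| Main outcome measure | 10, as a count and as a Z-score sum | not included |
| Analyses of longitudinal effect | one main outcome, with others secondary | secondary |

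**2. Ten against eleven within one section.** Ten variables give counts 0 to 10, which is eleven categories. The formula nevertheless takes n = 11 as the number of possible risk factors. With p = 0.25, the expected share of children with no risk factor is 0.75^10 = 5.6% for ten factors and 0.75^11 = 4.2% for eleven. The observed-to-expected ratios therefore depend on which is meant. The text does not say whether 11 counts the categories or brings PA level back in.

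**3. The plan's own constant.** k = (z0.975 + z0.80)² = (1.960 + 0.842)² = 7.85, against the stated 7.9. This confirms that the sample-size formula uses an undivided two-sided 5%. Table 3 also gives alpha as 5%.

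**4. Chance of at least one false positive when no outcome is affected.** Each test is taken at two-sided 5%. For m independent tests the chance is 1 − 0.95^m. For correlated tests, normal test statistics were simulated with equal correlation between outcomes and equal correlation between years. The document gives no correlations, so these are assumptions.

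*Reading A: any of the eleven variables, one year.*
- Independent: 1 − 0.95^11 = 43.1%.
- Correlation 0.3, 0.5, 0.7: about 37%, 30%, 22%.
- Without PA level (ten variables), independent: 1 − 0.95^10 = 40.1%.

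*Reading B: one composite.*
- One fixed time: 5%.
- Each of six years (2016 to 2021), independent: 1 − 0.95^6 = 26.5%.
- Each of six years, between-year correlation 0.5, 0.7, 0.8: about 21%, 17%, 14%.

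*Reading C, hypothetical worst case: every variable in every year, 11 × 6 = 66 tests.*
- About 50% to 92% over correlations of 0 to 0.7 between outcomes and 0.5 to 0.8 between years.
- Full independence would give 1 − 0.95^66 = 96.6%. These variables cannot reach that, because non-HDL is total cholesterol minus HDL (Blood samples section).

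All figures assume that each single test holds its nominal 5%. Clustering of children in nine schools is a separate matter and is not included.

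**The case against.** The strongest reply is that the article does describe one main outcome. The abstract can be read as naming one construct measured in several ways. The section headed Main outcome measure ends in one clustered score per child, and the longitudinal section models the main outcome in the singular. On that reading the risk is 5% at one fixed time.

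This has force against three stronger claims that a reader might infer.

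- *That the trial tests eleven separate primary outcomes at 5% each.* The 5% in Table 3 and in Intervention analyses is an input to sample size. No section makes it the rule for declaring any single outcome positive.
- *That a positive primary result is likely by chance.* For eleven outcomes in one year the chance is 22–43%, below one half. It passes one half only in the 66-test case, and no section says that every annual component test counts as a chance of success.
- *That the absence of a multiplicity rule is a fault.* Such a rule may stand in the full protocol or in an analysis plan that is not shown.

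The reply does not remove the contradiction. The composite reading still leaves two forms of the outcome, an unstated selection of factors, ten against eleven, no primary year, and an abstract that places PA level differently from the body. Condensing a longer document would explain omissions, but it does not explain conflicting statements.

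**Conclusion.** The point holds as an inconsistency in what is primary, and it should be corrected. It rests on the printed text alone: eleven variables with PA level in one section, ten without it in another, PA level secondary in a third, two forms of the composite, and no primary time.

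The consequence for error depends on the reading. It runs from 5% (one composite, one time), through about 14–21% (one composite in each of six years, with correlated years), to 22–43% (any of eleven variables in one year). All but the 5%, 26.5% and 43% figures rest on assumed correlations. The 66-test range shows only how far the ambiguity could stretch and should not be quoted as the trial's error rate.

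**What to change.** 1. Name one primary outcome. The age- and sex-standardised clustered Z-score is a natural candidate. List its components. In doing so, decide whether total cholesterol, HDL and non-HDL should all enter, since the third is the difference of the first two. Note also that five of the ten variables need blood, which 1344 of 2297 children gave at baseline.
2. State one estimate for it: the arm difference from the mixed model in Analyses of longitudinal effect, either at one stated follow-up time or as one stated longitudinal contrast. The choice matters for numbers. All six grades can contribute in 2016, but by 2021 only the 2015 first grade remains (351 children at baseline, 248 intervention and 103 control).
3. Make the individual components, the risk-factor count and the other annual comparisons supportive.
4. Class PA level once, and align the abstract, Main outcome measure and Analyses of longitudinal effect. Correct the binomial formula or the variable list so that ten or eleven is used throughout.

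The cost is mainly wording. The real price is that results on single components can no longer be claimed as primary.

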**Discussion:**

HOPP will provide evidence of effects on cardio-metabolic risk factors after a long-term PA intervention program in elementary schoolchildren. School-based PA intervention programs may be an effective arena for health promotion and disease prevention.

**Trial registration:**

The study is registered in Clinical trials (ClinicalTrials.gov Identifier: NCT02495714) as of June 20^th^ – 2015, retrospectively registered. The collection of baseline values was initiated in mid-January 2015.

## Background

Cardio-metabolic risk factors in childhood may act both as a measure of children’s health status, as well as a risk prediction of later illness. Several international studies have revealed increasing prevalence of adiposity in children and adolescents, and 41 million children younger than 5 years are estimated to be overweight or obese [1, 2]. In Norway, secular trends have shown an increase in adiposity, and a call for large scale monitoring of weight in children and adolescents has been proposed [3–5]. Hence, a significant proportion of children are at risk of developing lifestyle diseases as well as related emotional and psychosocial problems [1]. Lifestyle diseases earlier only seen in adults are wide spreading amongst adolescents, and even children [1]. In an attempt to counteract the immense lifestyle related problems worldwide preventing strategies have emerged [6].

There are few arenas where all layers of the population may be reached when implementing preventive measures to reduce sedentary lifestyle. To enhance physical activity (PA) and promote healthy behaviour, elementary schools are suitable arenas to reach all children [7]. Several studies have combined PA interventions with a pedagogic approach in elementary schools around the world [7–10] These studies have indicated a positive effect in terms of reduced overweight and associated diseases, as well as improved cognitive function and mental health [4, 11–18].

Most children spend a large part of their daily life at school, and schools offer a unique opportunity to promote health and wellbeing among *all* children with different socioeconomic background. The use of a school-based PA program may be an important tool to provide health promotion and disease prevention. Based on previous research a well-designed school-based PA intervention trial with a longitudinal design measuring health-related factors with a sufficient number of participants over a long time-period is overdue.

In 2014, politicians in Horten municipality, Norway, initiated a health promotion program for children called the Health Oriented Pedagogical Project (HOPP). HOPP was initiated in response to an increasing prevalence of obesity, inactivity and lifestyle related diseases in the local child population. The main objective is to evaluate the effects of a school-based PA intervention program on cardio-metabolic risk, offering a proxy for later non-communicable disease. Secondary objectives include assessment of physical, psychological and academic performance variables (Fig. 1).

**Fig. 1 Fig1:**
[figure not shown]
Overview of the thematic areas in the HOPP-project

## Methods/design

### Study population and inclusion criteria

The HOPP study is a controlled longitudinal school-based PA intervention. Seven elementary schools in Horten municipality, Vestfold County, Norway are intervention schools. Two control schools in Akershus County, Eiksmarka school (*n* = 520) and Rasta school (*n* = 465), were included. The control schools were recruited based on estimated socioeconomic level, using a centralised Norwegian program for systematic quality work in schools and kindergartens called PULS. This represent a total population of 2817 pupils of which 1815 children received the intervention as a part of the pedagogical platform in Horten municipality. All children were invited to be part of the research project. Based on recruitment procedures a total baseline participation of 2297 pupils (82%) was achieved. The children were recruited from 1^st^ - 6^th^ grade (age 6–11 yrs) (Table 1).

**Table 1 Tab1:** Baseline population for all grades as of 2015 is shown, as well as the sample size, based on children whose parents gave consent to participation in the research project

Grades	1	2	3	4	5	6	Total
Population	457	484	457	462	461	496	2817
Sample	351	381	370	389	381	425	2297
Intervention schools	248	264	229	264	269	271	1545
Control schools	103	117	141	125	112	154	752

The sample size is divided into intervention and control schools

### Information and recruitment

The school-based PA program was compulsory and implemented as a new pedagogical standard within the Horten municipality. An information campaign about HOPP was performed by Horten municipality in 2014, including written information with informed consent to parents, pamphlets, social media interaction and a website. In addition, the study team gave oral and written information to parents at school meetings. No information about the school-based PA program was given to control schools.

### Intervention

The main aim in HOPP is to reduce cardio-metabolic risk factors in elementary school children by increasing PA in school as part of the pedagogical approach. As elementary school is compulsory, children from all socioeconomic layers will be reached. The implementation is low cost as both physical (school facilities) and human (teachers) resources are already available.

A working group of 14 experienced teachers (two from each school) in Horten municipality with special interest and education in health promotion and PA, as well as pedagogical experience were assembled. Harter’s Competence Motivation Theory was the theoretical basis used by the working group [19, 20]. The theory is achievement motivation based, and founded on a person’s feelings of personal competence. According to the social learning theory of Bandura, self-efficacy increases when a person successfully masters a task. This encourages the person to master more tasks. Embracing this theory, our school-based PA program is based on a constant development of mastery of the curriculum throughout elementary school [19, 20]. In HOPP, the educational program is re-structured from passive learning into active learning. Thus, using the natural potential in the child for PA to enforce academic skills and simultaneously promoting health.

The working group established a large library of activities emphasizing theoretical learning while being physically active, within language, mathematics and English subjects within academic guidelines for grades 1–7. The activities were based both on the teachers’ own ideas and proposals from The Norwegian Directorate for Education and Training (udir.no) and ideas from Trudvang Elementary School. The activities were adjusted for grade level and aimed to have moderate to high intensity level, with 25–30% of the time at a vigorous activity level.

“Activity boxes” according to the grade level were created following an eight months testing period. All boxes, located in each classroom, contained teaching material with the possibility of progression. After the eight months testing period, all 210 teachers in Horten municipality were trained in the new pedagogical approach enabling the use of PA in school lessons. This was done in spring 2015 by: ^1)^ a two-day gathering of all teachers, ^2)^ two dedicated teachers from the working group held follow-up courses at each school with regular intervals in spring 2015 and ^3)^ the municipality established a 100% position for a specially trained teacher to follow up all schools weekly during the whole project period (2015–2021).

In Norway, organised PA during elementary school consists of 90 min weekly physical education lessons. The HOPP intervention in Horten municipality consisted of additional 45 min of activity a day, replacing ordinary desk learning with physical tasks. Hence, the school-based PA program at the intervention schools involves an addition of 225 min/week of PA. Based on the “library” of activities in the toolbox, teachers decided individually when and how the activity lesson should be conducted. As a morning session in elementary school typically lasts 90 min before recess, a typical lesson often consists of 45 min of theory in classroom, then 45 min with active learning. The activities were performed in the schoolyard, gymnasium or in the school halls.

No individual follow-up of pupil’s participation in the intervention was completed. This implies that individual intensity level and absence from school are not recorded. However, teachers completed daily a questionnaire regarding the number of minutes of activity and intensity level of each class. Twice a year the questionnaires were collected. The control schools do not have any PA program or plans for establishing any program during the project period. The control schools upheld their 90 min/week according to the curriculum.

### Outcome measures

The tests were supervised by the principal investigator, and conducted by students from the Kristiania University College, Institute of Health Sciences, Oslo, Norway. All students were trained before administrating the tests. All tests were performed at the elementary schools.

All pupils in 1st to 6th grade (6–11 years) recruited in 2015 are followed longitudinally from baseline in spring 2015 for as long as they stay in elementary school. Hence, 1st grades in 2015 are followed until 2021, though 6th grade is followed for one year. This implies an annually decline in the number of participants in the research project as the eldest pupils moves on to junior high school (Fig. 2). The implementation of the intervention started fall 2015. Due to ^1)^ time limitations, ^2)^ the total test load at each grade and ^3)^ age specific tests, some tests were limited to certain age groups, as shown in Table 2. In Fig. 3 the cumulative number of all tests at each grade throughout the length of the study is shown.

